### Serious Adverse Events (SAE)

SAEs are to be reported to the TCC by the trial site within 24 hours of being notified, from consent and within 28 days from the completion of treatment [SABR, RFA, MWA, TARE, TACE] is completed/discontinued.

The investigator at the trial site is responsible for;

- grading the event according to the [NCI CTCAE vs 5](chrome-extension://efaidnbmnnnibpcajpcglclefindmkaj/https:/ctep.cancer.gov/protocoldevelopment/electronic_applications/docs/ctcae_v5_quick_reference_5x7.pdf)
- identifying the seriousness of the adverse event
- identifying the causal relationship to the treatment (see **Table 8: Definitions of causality**)
  - attribution to the SAE must be recorded in the patients’ medical records and reported on the SAE form
- identifying the causal relationship in relation to other medication
- determining the expectedness according to the Investigators Brochure (medicinal products)
- reporting to their local approving authorities as per local guidelines
- to follow-up the event until resolution or death

The initial SAE report should always include at least the following information; participant number, suspected medicinal produce if applicable, identifiable reporting source, description of medical event, seriousness criteria and causality assessment by the investigator. Remaining information must be forwarded to the TCC as soon as possible, but no later than 7 calendar days from the initial report.

The investigator is also responsible for notifying responsible HRECs, Research Governance Officers or other appropriate regulatory authorities of the SAE according to local ethical and regulatory guidelines. They are also to follow up the event (with regular reporting) until resolved.

The trial coordinating centre (TCC) shall;

- Implement and maintain a suitable recording system to record information from all SAEs received from Trial Sites.
- On receipt of an SAE, arrange for the trial chairpersons and/ or a clinical reviewer to review the event and confirm causal relationship and expectedness
- Report all SAEs to TROG Cancer Research
- Notify the sponsor (TROG Cancer Research) and all other participating investigators of any serious unanticipated related adverse events and any action taken
- Notifying the regulatory authorities of each country of any significant issue that has arisen from analysis of overseas reports or action that has been taken by another country’s regulatory authority in reporting timelines.

**Table 7: Definitions of causality**

| **RELATIONSHIP** | **DESCRIPTION** |
| --- | --- |
| Unrelated | There is no evidence of any causal relationship with the trial treatment |
| Unlikely | There is little evidence to suggest there is a causal relationship (e.g. the event did not occur within a reasonable time after administration of the trial treatment). There is another reasonable explanation for the event (e.g. the patient’s clinical condition, other concomitant treatment) |
| Possible | There is some evidence to suggest a causal relationship (e.g. because the event occurs within a reasonable time after administration of the trial treatment). However, the influence of other factors may have contributed to the event (e.g. the patient’s clinical condition, other concomitant treatments) |
| Probable | There is evidence to suggest a causal relationship, and the influence of other factors is unlikely |
| Definitely | There is clear evidence to suggest a causal relationship, and other possible contributing factors can be ruled out |

## New cancers

The development of a new non-HCC cancer should be regarded as an AE, or an SAE if they meet at least one of the serious criteria. New non-HCC cancers are those that are not the primary reason for the administration of the study treatment and have been identified after the participant’s inclusion in this study. They do not include metastases of the original cancer.

# STATISTICAL CONSIDERATIONS

## Sample Size Calculation

**Cohort 1:** HCC ≤3cm **and** eligible for percutaneous thermal ablation.

- From a review of the literature, we estimate a 2 year FFLP of 75% in the thermal ablation arm. A 20% difference in 2 year FFLP was considered clinically significant for this surrogate endpoint given the potential for local salvage and multiple subsequent lines of therapy. Assuming a 2-sided type 1 error rate of alpha=0.05, 47 evaluable patients per arm will provide 80% power to detect an absolute difference in 2 year FFLP of 20% (95% SABR versus. 75% thermal ablation). The required total sample size of 47+47=94 will be inflated to N=47/0.80=59 per arm to allow for a drop-out rate of 10% and a 2-year mortality rate of 10%. The required sample size is therefore estimated N=118.

**Cohort 2:** HCC >3cm **or** ineligible for percutaneous thermal ablation if ≤3cm.

- For the “treatment stage migration” cohort, we estimate a 2-year FFLP for the SOC therapies of 65%. Assuming a 2-sided type 1 error rate of alpha=0.05, a sample size of 40 patients per arm will provide 80% power to detect an absolute difference in event rates at 2 years of 25% (90% SABR versus 65% SOC). (16, 18, 57) Assuming a 10% drop-out rate and 10% mortality rate at 2 years the estimated number of patients per treatment arm is N=40/0.80=50 per arm (SABR or SOC). The required sample size is therefore estimated N=100.

## Sequence Generation

Randomisation for both patient groups will be performed using random block sizes of 6 and 4 to help ensure minimal imbalance in the size of treatment groups for each patient cohort.

To prevent imbalance in disease severity and HCC BCLC stage, stratified block randomisation using two factors will be used for SABR vs SOC cohorts (see **Section 5.4.2 Randomisation Treatment Allocation**).

## Endpoint Definitions

**Table 8: Endpoint definitions**

|  | **ENDPOINTS** | **MEASURES** |
| --- | --- | --- |
| **PRIMARY:** | 2-year FFLP | Local target lesion progression in Cohort 1 and Cohort 2 defined by mRECIST and RECIST v1.1 as outlined above in Section 8.1 **Definition of Progression*** |
| **SECONDARY:** | 2-year PFS | Local progression or the development of new intrahepatic or extrahepatic lesions as defined in Section 8 DISEASE PROGRESSION |
|  | 2-year OS | Death from any cause |
|  | Safety and adverse events | Cumulative incidence CTCAE v5.0 |
|  | Patient reported outcomes | EORTC QLQ-C30 and QLQ-HCC18 - mean scores over time. Time to ≥10 point decrease in the combined GHS/QoL score. |
|  | Health economic comparisons | Costs cost per QALY gained for SABR compared with PA/SOC at two years |

* If the estimated treatment effects for FFLP are similar for the 2 cohorts we will also perform an additional secondary analysis for FFLP in which data from the 2 cohorts are combined. With 218 patients and an overall event rate of 15% in the combined population, this sample size will provide 90% power to detect a hazard ratio=2.0 at alpha=0.05.

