## Objectives

**Table 2: Objectives and Endpoints**

|  | **OBJECTIVE** | **ENDPOINT** |
| --- | --- | --- |
| **PRIMARY** | Evaluate the efficacy of SABR compared to SOC first line therapies in terms of local lesion control | 2-year FFLP according to mRECIST ( or RECIST v1.1 when mRECIST can’t be used) |
| **SECONDARY** | Evaluate progression-free survival | 2-year PFS |
|  | Evaluate overall survival | 2-year OS |
|  | Evaluate safety and adverse events | Cumulative incidence of adverse events (CTCAE v5) |
|  | Compare patient reported outcomes between SABR and SOC therapies | EORTC QLQ-C30 and QLQ-HCC18 - mean scores over time. Time to ≥10 point decrease in the combined GHS/QoL score. |
|  | Cost-effectiveness analysis | Incremental cost per outcome (additional patient with FFLP at 2 years; and quality adjusted life years) for SABR compared with SoC. |
|  | Qualitative review of patient experience | Patient treatment experience assessed by qualitative methods |
| **EXPLORATORY** | To identify biomarkers associated with treatment outcome. | Changes in serum AFP, haematological and liver function parameters post-treatment. |

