# DISEASE PROGRESSION

Participants will undergo regular tumour assessment (multiphase contrast-enhanced CT or MRI of the liver) as per **Table 5: Schedule of Assessments** until disease progression, withdrawal, end of trial, or death, whichever occurs first. See **APPENDIX 3: Imaging Guidelines** for recommendations on specific imaging sequences.

- Baseline tumour measurements must be undertaken prior to any protocol treatment commencing. (see **Figure 2: mRECIST assessment of tumour lesions at baseline** for target lesion definition). The initial assessment of response will be determined after all protocol treatment has been completed, irrespective whether all of the planned treatment was delivered.
- The target lesion is to be assessed by mRECIST and RECIST v1.1 criteria (see sections **8.1 Definition of Progression** and **8.2 Definitions of (non-PD) target lesion** responses and **Figure 3: mRECIST assessment of tumour response**) at each applicable follow-up timepoint until progression.

Local progression is defined as at the first timepoint that either mRECIST **or** RECIST v1.1 criteria for progression are met. In addition, for cohort 1 (thermal ablation verses SABR) local progression will include the development of any new lesions within 10mm of the ablation cavity following thermal ablation or within 15mm of the target lesion following SABR.

In the event of a progression event, or if the investigator is in doubt as to whether progression has occurred, the imaging should be submitted for central radiological review and no further therapy undertaken until unequivocal progression has been confirmed. Repeat imaging at the next scheduled assessment, or sooner if clinically indicated, is recommended for equivocal findings. If subsequent repeat imaging confirms unequivocal progression the date of the initial imaging will be used as the date of progression. Please refer to section 14.7.4 for further details.

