## Statistical Analysis Plan

A statistical analysis plan (SAP) will be finalised prior to datalock and contain additional detail on the methods described below.

All analyses will be performed according to an intention-to-treat protocol, with a per-protocol analysis performed as a sensitivity analysis. For the FFLP, PFS, TTP, ORR and OS endpoints, analysis will be performed comparing 2-year estimates from cumulative incidence (FFLP) and Kaplan-Meier survival curves (PFS and OS). The two comparisons between groups (SABR vs. MWA/RFA and SABR vs. SOC) will be analysed separately. Secondary analysis using Gray and log-rank tests will be performed to evaluate differences in overall time to event distributions. Fine and Gray, Cox proportional hazards regression will used to estimate hazard ratios with 95% confidence intervals. Secondary outcomes including the EORTC QLQ-C30 and QLQ-HCC18 (presented as mean scores over time) will be assessed using linear mixed-effects models to account for repeated measures. Additionally, time to deterioration (TTD) of combined GHS/QoL will be analysed. TTD will be defined as the time to first onset of a ≥10 point decrease from baseline. A 2-sided type-1 error rate of alpha=0.05 will be used for all hypothesis testing. All analysis will be performed using Stata software (version 17).

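### Table 8 leaves death out of the PFS events, which conflicts with the endpoint's name, its Kaplan-Meier analysis and the separately listed TTP

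*Protocol*

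**What the plan says.** **Definition.** Table 8 in Section 14.3 describes 2-year PFS as "Local progression or the development of new intrahepatic or extrahepatic lesions as defined in Section 8 DISEASE PROGRESSION". The next row, for overall survival (OS), reads "Death from any cause". That is the only row of the table in which death is named as an event.

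**Cross-reference.** Section 8, to which the PFS row points, defines progression on imaging. It mentions death only as one of the points at which tumour assessment ends: "until disease progression, withdrawal, end of trial, or death, whichever occurs first".

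**Other mentions.** Table 2 (Section 2.2) has "Evaluate progression-free survival" as the objective and 2-year PFS as the endpoint, without an event list. The trial summary names PFS first among the key secondary objectives and does not define it.

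**Analysis.** Section 14.6 begins the relevant sentence with "For the FFLP, PFS, TTP, ORR and OS endpoints", so TTP stands beside PFS. TTP has no row in Table 2 or Table 8 and is defined nowhere. The methods are then assigned as "comparing 2-year estimates from cumulative incidence (FFLP) and Kaplan-Meier survival curves (PFS and OS".

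**Mortality.** Section 14.1 assumes 10% mortality at 2 years in each cohort, next to 10% drop-out. These figures serve only to inflate the FFLP sample size.

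**The concern.** PFS normally counts the first of progression or death. The event list in Table 8 counts progression only, which describes time to progression. A statistician who programs the endpoint from Table 8 and the estimator from Section 14.6 would produce a Kaplan-Meier curve in which a patient who dies without progression leaves the risk set as if progression could still be observed later. That curve would carry the PFS label and would lie above the true PFS curve whenever anyone dies without progression.

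The population makes such deaths possible: eligibility extends to Child-Pugh B7, and Section 1.4 discusses radiation-induced liver disease. Section 1.5 ranks PFS among the important secondary endpoints. At stake are the level of the reported 2-year PFS in each arm and, if deaths without progression differ by arm, the comparison between arms.

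**Working it through.** **1. The plan's own figure.** No PFS rate, event count or power is stated, so no PFS figure can be reproduced. The only calculation that uses the mortality assumption is the FFLP sample size. With two-sided alpha 0.05, 80% power and unpooled variance, n per arm = (1.960 + 0.842)² × [p1(1−p1) + p2(1−p2)] / (p1−p2)².

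- Cohort 1 (95% v 75%): 7.85 × (0.0475 + 0.1875) / 0.04 = 46.1, so 47. Then 47/0.80 = 58.75, so 59 per arm and 118 in total.
- Cohort 2 (90% v 65%): 7.85 × (0.09 + 0.2275) / 0.0625 = 39.9, so 40. Then 40/0.80 = 50 per arm and 100 in total.

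Both agree with Section 14.1. Neither depends on how PFS is defined.

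**2. The texts side by side.**

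| Place | What it implies about death in PFS |
| --- | --- |
| Table 8, PFS row | Not an event |
| Table 8, OS row | Named where it is meant to count |
| Section 8 | Ends tumour assessment; not an event |
| Endpoint name, Table 2 and summary | Suggests an event; no definition |
| Section 14.6, Kaplan-Meier for PFS, cumulative incidence for FFLP | Fits only if death is an event |
| Section 14.6, TTP listed as well | PFS should differ from TTP; under Table 8 it does not |

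The event list and the analysis section cannot both be followed and give a valid PFS.

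**3. Size of the effect if Table 8 is applied literally.** Let S be the 2-year Kaplan-Meier value with progression as the only event, and D the 2-year probability of death without progression. With independent hazards:

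- PFS as written = S
- PFS with death as an event = S × (1 − D)
- overstatement = S × D

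S is assumed at 50%, because the documents give none:

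| D | PFS with death counted | PFS as written | Overstatement |
| --- | --- | --- | --- |
| 5% | 0.50 × 0.95 = 47.5% | 50% | 2.5 points |
| 10% | 0.50 × 0.90 = 45.0% | 50% | 5 points |
| 20% | 0.50 × 0.80 = 40.0% | 50% | 10 points |

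For S from 40% to 90% the overstatement runs from 2.0 to 4.5 points at D = 5%, from 4 to 9 points at 10%, and from 8 to 18 points at 20%.

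**4. What the D values stand for.** The 10% is all-cause 2-year mortality in Section 14.1. Using all of it as D is right only if progression does not change the risk of death. If progression raises that risk, D is smaller, so 10% is an upper value on that figure. The 20% equals 100% minus the 80% 2-year OS of the ablation group in the local stage-migration series of Table 1; it too is all-cause mortality. As a check on the model, D can be read instead as the share of all patients whose first event is death, with 50% progressing first. Then the Kaplan-Meier value is exp(−H × P/(P + D)) with H = −ln(1 − P − D). For D = 5% this gives 48.4% against 45%, 3.4 points. For D = 10% it gives 46.6% against 40%, 6.6 points, although on the plan's 10% mortality this would require that nobody dies after progressing. The order of magnitude is the same.

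**5. Comparison between arms.** With S = 50% in both arms and D equal, both are overstated alike. If D were 5% in one arm and 15% in the other, PFS would be 0.50 × 0.95 = 47.5% and 0.50 × 0.85 = 42.5%, a difference of 5 points, while the written definition would show 50% in both. These unequal values are hypothetical.

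**The case against.** The best defence is that death was meant to count. The endpoint is called progression-free survival. Kaplan-Meier is paired with PFS and OS, while the competing-risk method is kept for FFLP. TTP is named as something else. The measures column of Table 8 is shorthand throughout, with no time origin or censoring rule in any row, and the analysis plan is to add detail on methods. This makes a drafting omission likely. It does not remove the defect: the protocol fixes the event list, and an analysis plan that adds death would contradict Table 8, while one that follows it would carry the omission forward.

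Some stronger readings are tempting and are not supported:

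- *The plan censors deaths.* No sentence says so. It follows only from combining the event list with Kaplan-Meier.
- *The overstatement is 5 or 10 points.* The 10% and 20% are all-cause mortality, not death without progression, and the 50% is assumed. In the randomised proton-versus-ablation trial described in Section 1.4, treatment-related late liver failure and death without progression or further treatment were not seen in either arm. That evidence is indirect (recurrent disease, protons), but it points to the lower end.
- *A survival cost would be hidden.* OS from any cause is a separate secondary endpoint with its own comparison, and the independent monitoring committee reviews safety data every 6 months. The cost would be missing from one curve only.
- *The comparison between arms is biased.* That requires deaths without progression to differ by arm, and nothing in the protocol shows that they will.
- *The result could not be compared with any other published PFS.* This turns on definitions in other studies, which the protocol does not give.

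**Conclusion.** The point holds as an error in a stated endpoint definition. Table 8 omits death from the PFS events, no other part of the protocol supplies it, and the omission is inconsistent with the endpoint's name, with the Kaplan-Meier analysis in Section 14.6 and with the separate TTP.

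The direction is certain if the text is applied literally and anyone dies without progression: 2-year PFS is too high. The size cannot be taken from the documents. Under independent hazards and an assumed progression-only value of 50%, it is 2.5, 5 or 10 points for 5%, 10% or 20% dying without progression, with 10% an upper value on the plan's own mortality figure.

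Severity is moderate. PFS is a secondary endpoint without stated power or a decision rule. The primary endpoint, the sample size and OS are untouched.

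**What to change.** In the PFS row of Table 8, write: *time from randomisation to first local, new intrahepatic or extrahepatic progression (Section 8) or death from any cause, whichever occurs first*. Kaplan-Meier in Section 14.6 then fits and can stay.

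In Section 14.6, either delete TTP, which no objective or endpoint table supports, or define it separately as progression alone with death as a competing event, estimated by cumulative incidence as for FFLP. Either choice resolves the overlap.

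The cost is one clause in Table 8, one edit in Section 14.6 and matching text in the analysis plan. Deaths are already collected for OS (Sections 7.5 and 11), so no new data or visits are needed. The change should be made before data lock.

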**Table 5: Definition of Local Progression by Cohort**

| **COHORT AND TREATMENT** | | **BASELINE MEASUREMENT** | **LOCAL PROGRESSION DEFINITION** |
| --- | --- | --- | --- |
| **Cohort 1**  **Comparison** | **MWA/RFA** | Ablation Cavity* | Within 10mm of ablation cavity |
|  | **SABR** | Target lesion | Within 15mm of target lesion |
| **Cohort 2**  **Comparison** | **SOC** | Target lesion | Target lesion |
|  | **SABR** | Target lesion | Target lesion |

*For RECIST V1.1 measurement

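### The pooled FFLP analysis is credited with 90% power for a hazard ratio of 2.0, but its stated inputs give about 51%

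*Protocol*

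**What the plan says.** The primary FFLP comparisons are made separately in each cohort (Protocol, Statistical Analysis Plan section). The footnote to Table 8 adds a pooled one: "If the estimated treatment effects for FFLP are similar for the 2 cohorts we will also perform an additional secondary analysis for FFLP". It then gives the size and power of that analysis: "With 218 patients and an overall event rate of 15% in the combined population", followed by "this sample size will provide 90% power to detect a hazard ratio=2.0 at alpha=0.05".

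Other sections supply the rest of the calculation. The Statistical Analysis Plan section says "A 2-sided type-1 error rate of alpha=0.05 will be used for all hypothesis testing". Randomisation Treatment Allocation sets 1:1 allocation in each cohort. Section 14.1 plans on 2-year FFLP of 95% against 75% in Cohort 1 and "90% SABR versus 65% SOC" in Cohort 2, and inflates both cohorts for 10% drop-out and 10% mortality at 2 years.

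**The concern.** In a time-to-event comparison, power depends on the number of events, not the number of patients. A 15% event rate in 218 patients yields few events, and a two-fold hazard ratio is too modest an effect to be found with 90% power from so few. The footnote's patient number, event rate, hazard ratio and power therefore cannot all hold together.

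What is at stake is how the pooled result will be read. Both cohorts are planned around much larger effects, so the pooled analysis is where a reader would look for evidence on a smaller one. If the protocol says that a two-fold difference would be found nine times in ten, a non-significant pooled result could be taken as fair evidence against it. On the footnote's own inputs such a difference would be missed about half the time.

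**Working it through.** **Inputs.** N = 218 (118 + 100), event rate 15%, hazard ratio 2.0 and power 90% come from the Table 8 footnote. Two-sided alpha of 0.05 comes from the Statistical Analysis Plan section. The 1:1 allocation comes from Randomisation Treatment Allocation.

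**Attempt to reproduce the 90%.** With the Schoenfeld formula and 1:1 allocation, power = Φ(√d × ln(HR)/2 − 1.960), where d is the number of events.

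- Events: 218 × 0.15 = 32.7.
- Power: √32.7 × 0.693/2 = 1.982, and 1.982 − 1.960 = 0.022, so power = Φ(0.022) = 0.509, about 51%.

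Other methods on the same inputs agree: Freedman 48%, a 20,000-run log-rank simulation 49%, and a two-proportion comparison at the matching rates (10.4% against 19.6%) 48%.

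**What 90% would need.** d = 4 × (1.960 + 1.282)² / (ln 2)² = 87.5, so 88 events. That is about 40% of 218 patients (88/218), or about 587 patients at a 15% rate (88/0.15).

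**What 33 events can detect with 90% power.** HR = exp(2 × (1.960 + 1.282)/√32.7) = exp(1.134), about 3.1.

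**With the plan's own losses.** Section 14.1 allows 20% non-evaluable: 218 × 0.80 = 174.4 patients, × 0.15 = 26.2 events, and power = Φ(1.773 − 1.960), about 43%.

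**Other readings of the footnote.**

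| Reading | Events | Power for HR 2.0 |
|---|---|---|
| As written | 32.7 | 51% |
| One-sided 0.05 | 32.7 | 63% |
| 15% is the SABR-arm rate | 46.6 | 66% |
| 218 patients per arm | 65.4 | 80% |
| 15% per year for 2 years | 60.5 | 77% |
| 15% per year for 3 years, everyone followed | 84.1 | 89% |

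Only the last comes close. The footnote does not give a yearly rate. Nor does that reading fit Section 14.1: 15% a year is about 28% at 2 years (1 − 0.85²), against the 18.4% below.

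**Is 15% the combined rate?** The Section 14.1 rates average (5% + 25%)/2 = 15% in Cohort 1 and (10% + 35%)/2 = 22.5% in Cohort 2. Weighted by size, (118 × 0.15 + 100 × 0.225)/218 = 40.2/218 = 18.4%. The stated 15% equals the Cohort 1 average alone.

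**How far a replacement figure depends on its assumptions.** Fix the hazard ratio at 2.0 and take 2-year events before losses.

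- Section 14.1 control rates kept (25% and 35%): SABR rates become 1 − √0.75 = 13.4% and 1 − √0.65 = 19.4%. Events = 59 × (0.25 + 0.134) + 50 × (0.35 + 0.194), about 50; power about 69%.
- Section 14.1 SABR rates kept (5% and 10%): control rates become 1 − 0.95² = 9.75% and 1 − 0.90² = 19%. Events = 59 × 0.1475 + 50 × 0.29, about 23; power about 39%.

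**The case against.** The strongest defence concerns reach. The sentence is a footnote to a conditional secondary analysis. The targets of 118 and 100 come from Section 14.1 alone, and no primary inference rests on the footnote. At the effects actually planned (hazard ratios of about 5.6 in Cohort 1, 4.1 in Cohort 2 and 4.6 pooled), even 26 events give about 97% power. All of this stands, and it limits the severity. It does not make the claim for a hazard ratio of 2.0 true.

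A second defence is longer follow-up. Imaging continues six-monthly after month 24, and the Cox and log-rank analyses could use later events. Assuming uniform accrual over 2 years, follow-up of 2 to 4 years, constant hazards and no losses, the Section 14.1 rates give about 56 events (74%), and its control rates with a hazard ratio of 2.0 give about 69 (82%). Neither reaches 90%, and neither is the 15% that the footnote states.

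A reader might infer that the right figure is about 59%, from 18.4% of 218, or 40 events. The documents do not support that: this event count arises only if the hazard ratios are about 4 to 6, so it cannot serve as the count under a hazard ratio of 2.0, and it ignores the 20% allowance.

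A reader might also infer that the pooling itself must change, because it depends on similar estimates and because Cohort 1 counts recurrences near the treated site ("Within 10mm of ablation cavity" for ablation, Table 5) while Cohort 2 counts the target lesion only. The cohort definitions are deliberate, and arms can be compared within cohort before pooling. The similarity criterion and stratification are details that an analysis plan commonly settles. These are design choices, not errors shown by this text.

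**Conclusion.** The 90% is wrong as written. The footnote's inputs give about 33 events and about 51% power for a hazard ratio of 2.0, a shortfall of about 39 percentage points, or about 43% power after the plan's 20% allowance. No reading that the text supports reaches 90%. Separately, the 15% does not match the roughly 18.4% implied for the combined population by Section 14.1. The result rests on the Schoenfeld approximation, 1:1 allocation, two-sided alpha of 0.05 and the 15% taken as the proportion with an event during follow-up.

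The severity is moderate. A reader might take the finding to mean that the trial is underpowered for its primary question; it does not show that, since the claim plays no part in setting 118 and 100.

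**What to change.** In the Table 8 footnote, either replace the 90% with what the stated inputs deliver (about 51% power for a hazard ratio of 2.0, or 90% power only at about 3.1) or delete the power claim.

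If the sponsor prefers a different event rate, the footnote should give the control-arm rates, the follow-up and the losses behind it, with the event count computed under the same hazard ratio that the power refers to. One example is the Section 14.1 control rates of 25% and 35% with a hazard ratio of 2.0: about 50 events and 69% power at 2 years before losses.

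The cost is a change of wording and a less favourable stated power. No patients, visits or data are added, and the primary sample sizes stay as they are.
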